**Figure 7. f7:**
[figure not shown]
Intervention activities conducted in each study arm. Abbreviations: ASCOT = the “Addressing the Social Determinants and Consequences of Tuberculosis” project; IEC = Information, Education, and Counselling; NTCC = Nepal National Tuberculosis Control Centre; TB = tuberculosis; UCT = unconditional cash transfer.

Following refinements by BNMT team and TSC inputs, recruitment will proceed. Again, when a study site reaches 32 recruited participants, recruitment will discontinue in that district. This provides ample allowance for completion of intervention activities and three surveys in 32 participants given the predicted attrition rate of ≤10% in the study sites.

The longitudinal survey data detailing participant feedback will form part of the process evaluation of the acceptability and feasibility of the ASCOT intervention. This will be supplemented by real-time self-reported ASCOT project feedback, and time and expense diaries of BNMT implementers, including DPCs and CHS. This data will be further complemented by the enhanced process evaluation aiming to evaluate health systems readiness and scalability of the ASCOT intervention. 

There will be multiple opportunities during the implementation of the pilot trial to assess for any harms or adverse effects. First, the longitudinal survey includes questions related to feedback from participants on the interventions received and involvement in the ASCOT project. Second, after each TB Club is conducted, participants will be asked to provide verbal and written feedback on the activities undertaken during the TB Club, including whether they perceive any of the activities to have caused harm or have the potential to cause harm. Third, issues relating to harm or adverse effects of the ASCOT project are included in the topic guides for KIIs and FGDs. All of these data will be analysed in real-time during the project and discussed between the ASCOT project team and where necessary the TSC to identify if any remediating actions are required. The criteria for discontinuing interventions include: participants who withdraw from the ASCOT project who, as an individual and inclusive of their household, will no longer receive the intervention; harm or adverse effect is identified that is felt by the project team and TSC to preclude continuation of interventions; and acts of God or unforeseen cuts to the study budget curtailing project activities.

**

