### Outcomes to be measured

**
*Co-primary outcomes*
**

The co-primary outcomes of the ASCOT pilot trial are acceptability and feasibility of the social, economic, and socioeconomic support interventions.

*Feasibility* will be measured using quantitative data including:

i) Recruitment (e.g. number of people invited, recruited, and participant attrition);ii) Fidelity to survey completion and the intervention (e.g. adherence to and completion of socioeconomic support delivery including receipt of cash transfers and attendance at TB Club amongst intervention arm participants); andiii) ASCOT staff time and costs plus overall project costs.

*Acceptability* will be measured using mixed-methods including:

i) Quantitative analysis of the implementer and participant satisfaction form;iii) Thematic analysis of the qualitative FGD and KII data within Sekhon’s Framework for healthcare interventions and quantitative analysis of the brief questionnaire completed prior to FGDs will include evaluation of health systems readiness and scalability
^
50,
51
^.

**
*Secondary outcomes*
**

Unpowered, exploratory secondary outcomes will compare the proportion of people with TB in each study arm by rates of:

*TB treatment success:* NTP-defined outcome of completed TB treatment or confirmed cured documented in TB register.
*Catastrophic costs:* TB-affected households that incur total out-of-pocket expenses and lost income during TB illness that equated to more than 20% of the same household’s annual pre-TB income.
*Wellbeing:* measured by self-reported levels of stigma, depression, and quality of life at six-month follow-up adjusted for baseline.

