**Secondary exploratory outcomes analyses**

Key quantitative survey data will include TB-related costs, stigma, mental health, and quality of life. This will be supplemented by TB treatment outcome data from the National TB Program register.

As per our related research, WHO TB Patient Costs Survey methods will be used to calculate total direct costs, lost income, and catastrophic costs (total TB-related costs of more than 20% of the same household’s annual pre-TB income)
^
38
^. TB treatment outcomes will be collated from National TB Program registers and will be aggregated to TB treatment success (the sum of the National TB Program defined outcomes of “Treatment completion” and “Cure”) vs no TB treatment success (the sum of all other National TB Program defined outcomes including “Lost to follow-up”, “Death”, “Treatment Failure”, “No evaluation”, “Change to drug-resistant TB regimen” and “Transferred out”).

Stigma will be measured by locally developing stigma score for the Nepali context by adapting elements of the validated Van Rie stigma scale, which comprises ten stigma-related questions with 5-point Likert scale responses. Each response category of the scale will be assigned scores of: -2: strongly disagree, -1: disagree; 0: neither agree nor disagree; +1: agree, and +2: strongly agree. The total scores will range from -20 (no stigma) to +20 (highest levels of stigma). A threshold of equal or above the median cohort stigma score will also be used as a binary classification of stigma.

Mental health will be measured using an adapted version of the Patient Health Questionnaires, PHQ-9, which has been validated in Nepal. The tool explores anxiety, depression, wellbeing, and discrimination through nine questions with four-point scale responses of 0: not at all, 1: sometimes, 2: usually, and 3: always. The range of scores is from 0 to 27 and the following categorisations have been used in the validated tool: 1–4 minimal, 5–9 mild, 10–14 moderate, 15–19 moderately severe, and 20–24 severe depression level. A threshold score of equal or above 10 will also be used as a binary classification of depression.

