Quality of life will be assessed using the EQ-5D-5L index. EQ-5D-5L uses five dimensions of quality of life: mobility, self-care, usual activities, pain or discomfort, and anxiety or depression. Each question includes a five-category response scale from 1: no problem, 2: slight problem. 3: moderate problem, 4: severe problems, 5: being unable. The EQ-5D-5L has not been validated in Nepal but has been validated in neighbouring India. Since Nepal and India share common sociocultural conditions and geographical features, we will calculated quality of life scores from the Nepal data using the validated value sets and weightings from India as estimates. The EQ-5D-5L also includes a health rating covariate measured on a scale of 0 to 100 based on participants' self-reporting. The participants are asked to choose an appropriate point that best defines their health condition for that day and to label it with a mark on the scale printed in the survey with 0 indicating lowest/poorest health and 100 indicating highest/best health.

Descriptive statistics will be used to analyse the quantitative survey data collected during household visits. In line with our own and others’ related research, the arithmetic means and 95% confidence intervals of patient costs data that is continuous in distribution will be described regardless of the distribution of the data, and any direct expenses, lost income, or annual income recorded as “zero” or missing will be replaced with the mean cost of each costs category (unless >10% of data for a particular variable is missing)
^
5,
6,
53
^. Nepalese rupees, the local currency, will be converted to United States Dollars according to
OANDA rates at the time of data collection. Continuous stigma and quality of life data will be summarised by median and IQR or mean and SD depending on distribution. Categorical data will be summarised as proportions with 95% confidence intervals. Continuous data relating to costs, stigma, mental health, and quality of life scores (including self-rated health) will be compared across study arms where relevant using the Kruskal-Wallis test or one way ANOVA with p values <0.05 considered significant. Proportions of participants above and below the binary thresholds of treatment success, catastrophic costs, stigma, and depression will be summarised and compared across study arms where relevant using a Chi-2 test with p values of <0.05 considered significant.

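### Filling missing cost and income values with a single mean, then analysing them as observed, makes each cost variable's 95% confidence interval too narrow by about the share filled (at most about 10%) and can misclassify catastrophic costs

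*Protocol article*

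**What the plan says.** The rule is in the protocol article, Data analysis and statistical plan, under Secondary exploratory outcomes analyses. It covers three kinds of field: direct expenses, lost income and annual income. The sentence begins with entries of zero and continues: "or missing will be replaced with the mean cost of each costs category (unless >10% of data for a particular variable is missing". The same paragraph reports continuous patient costs as arithmetic means with 95% confidence intervals, whatever their distribution. It adds that these costs "will be compared across study arms where relevant using the Kruskal-Wallis test or one way ANOVA with p values <0.05 considered significant". It does not say whether the mean is taken over all participants or within arm, and it mentions no adjustment for having filled values.

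Other parts of the article bear on how the rule would work:

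- **Outcome definition.** Outcomes to be measured defines catastrophic costs through "TB-affected households that incur total out-of-pocket expenses and lost income during TB illness" exceeding 20% of the household's annual income before TB.
- **Attrition.** Sample size and statistical power reports less than 5% in earlier research and expects similar rates. Study arms and activities plans "given the predicted attrition rate of ≤10% in the study sites".
- **Treatment outcomes.** Outcomes other than success include "Lost to follow-up”, “Death”, “Treatment Failure”, “No evaluation”, “Change to drug-resistant TB regimen” and “Transferred out". None is exempted from the filling rule.
- **Withdrawal.** Under Recruitment of people with TB and their households, individual data of participants who withdraw are deleted.
- **Visits.** Household visits for all participants fall at 2 to 4, 8 to 12 and 20 to 24 weeks after the start of treatment. Family members may be interviewed where appropriate.

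**The concern.** Single mean filling gives every incomplete record the same value and then counts it as an independent observation. Three consequences follow.

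1. The confidence interval reports more precision than the data hold.
2. The between-arm comparison is affected in a way that depends on which mean is used, and the text leaves this open.
3. Annual income is the denominator of the catastrophic-cost ratio, so a filled income can change a household's classification.

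The wording also treats every blank alike. A blank because nobody knows the cost and a blank because no cost could arise after death or stopped treatment would receive the same mean, although the outcome definition counts only what the household incurred.

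Patient cost data are the stated reason for wanting about 100 participants, and the pilot is meant to inform a larger trial with catastrophic costs among its outcomes. Cost estimates and their precision are therefore likely to be carried forward.

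**Working it through.** The article gives no interval width, standard deviation or missing share for costs, so there is no figure of its own to reproduce. The standard deviation cancels in the ratio below.

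**Inputs.** N = 128 in four arms of 32 (Abstract); rule active up to 10% missing per variable; attrition below 5% (sample size section) or at most 10% (Study arms and activities).

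**Cap.** 12/128 = 9.4% is within the rule; 13/128 = 10.2% is outside it. At most 12 values per variable can be filled.

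**Interval width.** Let k of n values be filled with the mean of the n − k observed values, which have standard deviation s.

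- Standard error as planned: s·√[(n−k−1)/((n−1)·n)]
- Standard error the observed data support: s/√(n−k)
- Ratio: √[(n−k−1)(n−k)/((n−1)n)], about 1 − k/n

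For 6 of 128: √[(121×122)/(127×128)] = √(14,762/16,256) = 0.953. For 12 of 128: √[(115×116)/(127×128)] = √(13,340/16,256) = 0.906. With the t quantiles applied:

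| n | filled | share | interval too narrow by |
|---|---|---|---|
| 128 | 1 | 0.8% | 0.8% |
| 128 | 3 | 2.3% | 2.4% |
| 128 | 6 | 4.7% | 4.8% |
| 128 | 12 | 9.4% | 9.5% |
| 32 | 1 | 3.1% | 3.3% |
| 32 | 3 | 9.4% | 9.9% |

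The comparison is with the observed-case interval. Against the interval that complete data would have given, the narrowing is about half: 2.4% for 6 of 128 and 4.8% for 12 of 128.

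**Coverage.** This was simulated with 40,000 replicates, values missing completely at random, n = 128, and 6 or 13 values filled (13 is one more than the cap allows). With normal costs, nominal 95% coverage is 93.7% and 92.3%. With lognormal costs (log-SD 1, an assumption) it is 91.0% and 89.3%, but the observed-case interval itself covers only 92.0%. The filling therefore accounts for about 1 and 3 percentage points; the rest is skew.

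**Between-arm test.**

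- *Pooled mean.* A share m filled in every arm turns an arm mean into (1−m)·(observed arm mean) + m·(pooled mean), so differences between arms are multiplied by 1 − m. With 3 of 32 filled in each arm this is 29/32 = 0.906. Simulated type I error of one-way ANOVA at 10% missing was 4.4% (log-SD 0.7, an assumption), so it is not inflated.
- *Within-arm mean.* With 3 of 32 filled per arm, the F statistic is multiplied by (32/29)×(124/112) = 1.22. For normal costs the chance of exceeding the 5% critical value is then about 9.3%. The simulation with log-SD 0.7 gave 9.0% at 10% missing and 6.2% at 5%.

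Kruskal-Wallis, which the plan also allows, was not simulated.

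**Catastrophic costs.** Let C be a household's total cost, Y its true annual income and M the mean used to fill. The true classification is C > 0.2Y; the filled one is C > 0.2M. A household poorer than average (Y < M) with 0.2Y < C ≤ 0.2M is recorded as not catastrophic when it is. A household richer than average with 0.2M < C ≤ 0.2Y is misclassified the other way.

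**Costs that do not apply.** Suppose a share d of participants truly had no cost in a category and all were given the mean of the others. The category mean is then overstated by d/(1−d): 2.0% at d = 2%, 5.3% at 5% and 11.1% at 10%. The article gives no value for d, and these are upper figures because such participants may have had part of the expense.

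**The case against.** The strongest reply is that the effect is small, bounded and confined to outcomes that the article itself calls unpowered and exploratory. Feasibility and acceptability, the co-primary outcomes, are untouched. The 10% exception caps the narrowing. The rule also follows the team's cited earlier work, which has value for comparability. All of this stands, and it limits the priority.

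Some stronger readings are tempting but not supported:

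- **That intervals will be 5 to 10% too narrow.** This is the upper half of a range that starts at 0. Attrition is also not the same as the share filled: withdrawn participants are deleted rather than filled, while item non-response adds to it.
- **That type I error is inflated.** This needs a within-arm mean. The text speaks of the mean of each cost category and mentions no arm. On that plainer, pooled reading there is no inflation, only dilution of differences.
- **That people who died or stopped treatment are charged costs they never had.** The article does not show this. The visits are household visits for all participants, so someone who stopped treatment can still be surveyed, and family members may answer. How fields that do not apply are coded is not given. The text supports only that nothing in the rule prevents it.

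It may also be said that counting only incurred expenses makes early death or stopping look cheap. That is fair, and the remedy has to deal with it. Finally, the same sentence also replaces recorded zeros. That is a separate and potentially larger problem, because the 10% limit as worded counts only missing data. Correcting the treatment of zeros alone would leave the present point in place.

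**Conclusion.** The point holds in a limited form. As written, the rule gives a 95% interval for each cost variable that is too narrow by about the share filled, from 0 to just under 10% for the whole sample. No assumption about the standard deviation is needed; the coverage figures also assume that values are missing completely at random. For total cost the narrowing is smaller when only some categories are missing.

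The effect on between-arm tests depends on a choice that the article leaves open: attenuation with a pooled mean, excess false positives with a within-arm mean. Misclassification against the 20% threshold is a direct possibility whenever income is filled, but its frequency cannot be worked out from the article. Assigning costs that were not incurred is a possible result of applying the rule literally, not a documented one. The change is worth making because it is cheap and the estimates will inform the next trial, but it is not urgent.

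**What to change.** 1. Drop single mean filling of missing values as the main analysis. Either report observed-case means and intervals, or use multiple imputation, deriving total and catastrophic costs within each imputed set and combining them by Rubin's rules. The observed-case route is affordable: 128 are recruited to secure 100 with complete data, and 10% attrition leaves 128 × 0.90 = 115.
2. Separate unknown from not applicable. Do not impute direct treatment expenses for periods known to fall after death or after treatment stopped. Report costs alongside treatment outcome, so that early death or stopping is not read as a saving.
3. Keep the present rule as a sensitivity analysis for comparability with the team's earlier reports, and state there whether the mean is pooled or within arm.

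The cost is revised analysis wording, modest extra programming in Stata and slightly wider intervals. The main results will be less directly comparable with earlier mean-filled figures, which the sensitivity analysis covers. No new data are needed.

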### Plans for dissemination of study findings

The intended research outputs of this work are to: i) present the interim and final findings at the International Union Against TB and Lung Disease in November 2022 and 2023 respectively; ii) publish, in 2023, two first-author papers in PubMed citable, peer-reviewed, open-access journals concerning the ASCOT pilot trial; iii) consolidate partnerships with and disseminate findings to key stakeholders (including NTP and TB civil-society), Social Protection Action Research and Knowledge Sharing network (SPARKS,
www.sparksnetwork.ki.se) and WHO; and submit a strong application that receives large-scale funding to conduct a well-powered full-scale ASCOT trial that evaluates the impact of the intervention on health and socioeconomic outcomes.

### Study status

From August to December 2021, training of BNMT DPC, CHS, and FCHVs took place in the field. In January 2022, recruitment, activities, and the intervention were piloted in 10–20 participants and the initial implementation successes and challenges discussed amongst the project team. Recruitment of consecutively newly diagnosed people with TB in the study sites and key stakeholders continued until September 2022. Write up and dissemination, including a one-day workshop and dissemination meeting of ASCOT team and key stakeholders including the NTP, will be completed prior to the study end date of 31
^st^ March 2023.

## Discussion

The ASCOT pilot trial extends our Wellcome Trust Seed Award research with diverse stakeholders in Nepal and internationally. This intersectoral participation and broad dissemination through academic meetings, networks such as SPARKS, and partnerships with WHO will continue to ensure the widest possible use of our research findings. Outputs will include publications in leading peer-reviewed scientific journals, media pieces, policy guidance, and a practical handbook on implementing socioeconomic support for TB-affected households. 

The further significance of the study lies in refining a socioeconomic support intervention for TB-affected households in Nepal that is locally-appropriate, feasible, and acceptable. Through collaboration with diverse stakeholders in Nepal from patients to NTP managers to civil-society representatives, it is envisaged that this work will lead onto a successful funding bid for the definitive, well-powered randomised-controlled ASCOT trial, which will evaluate the impact of the intervention on outcome measures including catastrophic costs and TB treatment outcomes.

## Conclusions

Ending TB, alleviating poverty, and eradicating catastrophic healthcare costs are integral aspects of WHO’s global TB policy and the SDGs. This highly timely pilot and future trial will provide the world’s first, robust evidence regarding the feasibility, acceptability, and impact of socioeconomic support for TB-affected households in a TB-endemic LIC. Strong national and international partnerships, collaborations, and networks, will ensure the findings lead to policy and practice change in Nepal and other LICs.

## Data Availability

No underlying data are associated with this article Open Science Framework: Addressing the Social Determinants and Consequences of Tuberculosis in Nepal (ASCOT): a pilot trial.
https://doi.org/10.17605/OSF.IO/U5V72
^
19
^ This project contains the following extended data: ASCOT CONSENT FORM FOR PARTICIPATION IN SURVEY AND PILOT TRIAL V5.2_27-01-2022_English.pdf ASCOT household contact consentform V5_27-01-2022_English.pdf ASCOT KII and Workshop ConsentForm v4.1 27-Jan-2022_English.pdf ASCOT FGD and workshop consentform-v4.1-27-Jan-2022-English.pdf ASCOT FGD and workshopparticipant information sheet V4.1-27-01-2022.pdf ASCOT KII and workshopparticipant information sheet-V4.1-27-01-2022 English.pdf ASCOT survey and pilot trial participant information sheet-V5-27-01-2022.pdf Household contact pilot trial participant information Sheet v4.1 27 Jan 2022.pdf ASCOT Tuberculosis InformationLeaflet v3-27-01-2022_TW.pdf JGHT ASCOT Survey v5.1 27-01-2022.pdf ASCOT FGD and KII TopicGuides_v4.0 27012022-PR_BR_KD_TW_Clean.pdf ASCOT Protocol v4.3 27012022 TW.pdf ASCOT SOP v11.3 27012022 TW.pdf Nepali_version_Final-v5.231_Jan_2022_Patient cost instrument_(Nepal)_ASCOT project-revised.pdf Data are available under the terms of the
Creative Commons Zero "No rights reserved" data waiver (CC0 1.0 Public domain dedication). Open Science Framework: SPIRIT checklist for ‘Protocol for the Addressing the Social Determinants and Consequences of Tuberculosis in Nepal (ASCOT) pilot trial’.
https://doi.org/10.17605/OSF.IO/U5V72
^
19
^
